**Subjects:** Men and women between the ages of 40 and 75 with visceral obesity and IGT will be recruited to participate. This age group has a higher prevalence of both visceral obesity and IGT.

Specific inclusion criteria are as follows: (a) adults between the ages of 40 and 75; (b) fasting glucose less than 120 mg/dl PLUS 2 hour postprandial glucose level during 75 gram OGTT between 140 – 200 mg/dl; (c) BMI > 27; and (d) increased waist circumference and/or increased waist-to-hip ratio (*see anthropometric measurements* below).

Subjects will be free of major medical illnesses such as uncontrolled hypertension, congestive heart failure or active malignancies. Women of child-bearing potential who are or plan to become pregnant or will breastfeed an infant will be excluded. Subjects taking corticosteroids or other medications that can significantly alter glucose metabolism will also be excluded. Groups will be matched on gender, BMI, estrogen status, and 2-hr glucose level (during screening OGTT). A third party investigator will be responsible for all randomization and coding of medications and placebo.

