#### EXPERIMENTAL DESIGN

After screening, 60 men and women who meet the criteria for study inclusion will be randomly assigned into 4 groups, with each group containing 15 subjects (n=15). The treatment period will start at week 0 and continue for 40 weeks total.  **During** **weeks 0-4**, *groups 1 and 2* will receive an oral placebo and *groups 3 and 4* will receive pioglitazone orally every day. **During weeks 5-40**, *group 1* will continue the oral placebo and self-inject a SQ placebo and *group 2* will continue the oral placebo and self-inject rhGH. Also **during weeks 5-40**, *group 3* will continue pioglitazone and self-inject a SQ placebo and *group 4* will continue pioglitazone and self-inject rhGH.

*Group 1* (n=15): Oral placebo plus SQ placebo.

*Group 2* (n=15): Oral placebo plus rhGH.

*Group 3* (n=15): Pioglitazone plus SQ placebo.

*Group 4* (n=15): Pioglitazone plus rhGH.

Sample size was determined using data from Johannsson et. al, 1997 in which a dose of rhGH comparable to ours was used to achieve a 17.9 +/- 3.5 percent change in visceral fat volume and an increase in insulin sensitivity of 1.2 +/- 0.6 mg/dl  hr over time (24). Using this information, we have powered our study based on 2 primary efficacy endpoints as follows: (a) 12 subjects (n=12) are needed *per group* in order to have an 80% chance of detecting a change in visceral fat volume of at least 17.9 percent, and (b) 15 subjects (n=15) are needed *per group* in order to have an 80% chance of detecting a change in insulin sensitivity of at least 17.6 percent. Therefore, our sample size for this study will be 15.

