#### STUDY ENDPOINTS

**Oral glucose tolerance test:** As per the technique described under screening, a 75 gram OGTT will be repeated at week 43, approximately 3 weeks after discontinuation of all study medications (washout period). In addition, the glucose area under the curve, or AUC, will be measured using the trapezoid method. Based on previously published data, we expect that rhGH administration will cause at least a 10% reduction in both postprandial glucose (2 hours post OGTT) and glucose area-under-the-curve compared to baseline values.

**CT of the abdomen:** A non-contrast CT of the abdomen to quantify visceral adiposity will be obtained at the baseline visit and again at week 40. This imaging technique is among the most reliable for measuring visceral fat (32). Scans will be

obtained at 5 levels: spleen/liver, L3-4 lumbar disc, L4-5 lumbar disc, lower edge of pubic symphysis, and upper thigh (with reference to edge of lower symphysis). The area of the visceral and subcutaneous abdominal fat compartments at the

5 levels will be measured and recorded in centimeters squared. Abdominal visceral volume will then be calculated (in liters) using the visceral tissue areas of the 5 scans and the measured distances between them. The same CT scanner will be used at the start and completion of the study, and the same radiologist at VA Palo Alto will analyze all scans.

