TZDs versus diet plus exercise: An alternative approach that might obviate the need for insulin sensitizer therapy is diet and exercise. However, this approach will not be used in this study for two reasons. First, many

viscerally obese, IGT adults have already tried diet and exercise and failed. Secondly, previous studies have shown that diet and exercise cannot overcome the transient insulin resistance and hyperinsulinemia associated with rhGH (44,45).

E. **METHODS OF DATA ANALYSIS**

   Data will be analyzed using StatView software for Microsoft Windows (SAS Institute Inc., Cary, NC). All data will be expressed as the mean +/- SE. A Student’s *t* test will be used to compare baseline values of the subject groups. For measurements pertaining to visceral fat, insulin sensitivity and glucose metabolism, ANOVAs for repeated measures will be used to analyze differences between data obtained at all time points. Area under the curve (AUC) for glucose data will be determined using the trapezoid method. In addition, results will be considered significant at *P* < 0.05.

F. **SIGNIFICANCE**

A. **Prevention of type 2 diabetes** **in viscerally obese adults with IGT**

The growing health care burden of type 2 diabetes mellitus in the U.S. demands that newer, more effective diabetes prevention strategies be implemented. One way to achieve diabetes prevention is to target adults who are at greatest risk for developing diabetes, such as viscerally obese adults with IGT.

Recent studies like the Diabetes Prevention Program (DPP) Trial indicate that, in individuals with IGT, interventions that result in visceral fat reduction also significantly reduce the risk of developing overt diabetes. Unfortunately, in non-experimental settings, many obese individuals have had little success in achieving visceral fat reduction with current weight loss modalities such as diet, exercise or anorexogenic drugs. This lack of success is often related to noncompliance and recidivism with diet and exercise and with limited overall benefit, intolerable side effects and/or addictive potential with anorexogenic medications. Furthermore, the potent weight-reducing effects of bariatric surgery are often eclipsed by severe gastrointestinal complications postoperatively and, in rare circumstances, an increase in mortality.

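### For outcomes with one baseline and one follow-up value, the planned repeated-measures ANOVA is a change-score test; baseline-adjusted ANCOVA uses the same data more efficiently

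*Protocol*

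**What the plan says.** Protocol section E (Methods of Data Analysis) sets one method for three families of outcome: "For measurements pertaining to visceral fat, insulin sensitivity and glucose metabolism, ANOVAs for repeated measures will be used to analyze differences between data", with all time points included and significance at P < 0.05. It names no contrast and no covariate.

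The Study Endpoints section gives the measurement times:

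- CT visceral fat: baseline and week 40.
- Insulin sensitivity test (SSPG): baseline and week 43.
- OGTT: screening, then a repeat at week 43.
- Fasting glucose: baseline and eight later visits.
- HbA1c: baseline and three later visits.

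Experimental Design sizes the trial on two endpoints, with an "80% chance of detecting a change in visceral fat volume of at least 17.9 percent" and an "80% chance of detecting a change in insulin sensitivity of at least 17.6 percent".

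Section D (Subjects) requires a "2 hour postprandial glucose level during 75 gram OGTT between 140 – 200 mg/dl" for entry. It matches the groups on gender, BMI, estrogen status and screening 2-hour glucose. Study Endpoints expects rhGH to produce "at least a 10% reduction in both postprandial glucose (2 hours post OGTT) and glucose area-under-the-curve compared to baseline values".

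**The concern.** Repeated-measures ANOVA suits fasting glucose and HbA1c, which have several visits. For the three outcomes with only two values it becomes a comparison of change scores. That fixes the weight on the baseline at one, whatever the correlation between baseline and follow-up. ANCOVA estimates that weight and, apart from its small degrees-of-freedom cost, is at least as precise. With 15 subjects per group, the precision lost on the two powered endpoints matters.

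A second issue concerns interpretation. The 10% expectation is phrased as a fall from baseline, but subjects enter because a 2-hour glucose reading was raised. If that reading also serves as the baseline, part of any later fall is regression to the mean and would occur without a drug.

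**Working it through.** **The plan's own figures.** Experimental Design gives 12 and 15 per group. It does not name the analysis behind them or give a baseline-to-follow-up correlation (rho). Reading the quoted +/- values as SDs, n = 2(1.96 + 0.84)² SD²/difference² gives 2 x 7.85 x (3.5/17.9)² = 0.6, so 1 per group for visceral fat. For insulin sensitivity it gives 2 x 7.85 x (0.6/1.2)² = 3.9, so 4 per group. The stated sizes are not reproduced this way, and no rho can be recovered from them. That is a separate matter; the check below uses variance ratios, which do not depend on it.

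**Step 1: equivalence.** With two time points, the group-by-time F equals the one-way ANOVA F on change. On a simulated data set both were 2.6534.

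**Step 2: variance.** With equal variance s² at both times:

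- Var(change) = 2s²(1 - rho)
- Var(ANCOVA) = s²(1 - rho²)
- Ratio = (1 + rho)/2

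**Step 3: degrees of freedom.** For k covariates, N = 60 and four groups, multiply the ratio by 1 + k/(N - 4 - k - 1). Baseline alone (k = 1) gives 1 + 1/54 = 1.0185. Baseline plus four uninformative matching factors (k = 5) gives 1 + 5/50 = 1.10. Rho is assumed.

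| rho | (1 + rho)/2 | baseline only | 15 per group acts like | baseline + 4 uninformative factors |
|---|---|---|---|---|
| 0.5 | 0.75 | 0.76 | 19.6 | 0.83 |
| 0.7 | 0.85 | 0.87 | 17.3 | 0.94 |
| 0.8 | 0.90 | 0.92 | 16.4 | 0.99 |
| 0.9 | 0.95 | 0.97 | 15.5 | 1.05 |

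Simulated 15 v 15 comparisons agree. At rho 0.5, 0.7, 0.8 and 0.9 the change score had 77% power throughout, and ANCOVA on baseline had 86%, 82%, 79% and 77%. With four uninformative factors added, a two-group model fell to 80%, 75%, 72% and 71%. With factors explaining 15% of residual variance, it gave 87% at rho 0.5 and 78% at rho 0.9. Type I error was 4% to 6% for every method.

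**Step 4: selection on 2-hour glucose.** The expected untreated fall is (1 - rho) x (mean of those selected - source mean). Source mean, SD and rho are assumptions; the 140-200 mg/dl window is from the Protocol.

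- Mean 120, SD 35, rho 0.5: selected mean 159.7; fall 0.5 x 39.7 = 19.9 mg/dl, or 12.4%.
- Mean 130, SD 35, rho 0.7: selected mean 161.6; fall 0.3 x 31.6 = 9.5 mg/dl, or 5.9%.
- Mean 140, SD 40, rho 0.85: selected mean 164.9; fall 0.15 x 24.9 = 3.7 mg/dl, or about 2%.

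At mean 130 and SD 35, a simulated placebo group of 15 reached within-group P < 0.05 in 45%, 27% and 15% of runs at rho 0.5, 0.7 and 0.85.

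**Step 5: between-group contrast for the same outcome.** In those simulations both methods were essentially unbiased (error at most 0.2 mg/dl). Standard errors were 11.5, 9.4 and 6.8 for change and 11.3, 9.5 and 6.9 for ANCOVA. Selection narrows the baseline range, so there is little for the covariate to explain.

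**The case against.** The planned test is not invalid: its type I error is sound and the cost is precision, of a size that cannot be fixed without rho. CT uses the same scanner and the same radiologist throughout, so rho for visceral fat could be high and the gain small. Both points stand. Choice of covariates is also commonly left to a statistical analysis plan, so silence about the matching factors is not in itself a fault. But section E is not silent on the method. It names one, and for these outcomes a better one is available from data already collected.

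A reader might infer more than the documents support:

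- *That ANCOVA is what removes regression to the mean.* Any randomised between-group contrast does so on average, including the group-by-time test.
- *That adding every matching factor must help.* With uninformative factors the variance ratio reaches about 1.05 at rho 0.9.
- *That the plan compares time points rather than groups, or relies on the group main effect.* The latter would average in the untreated baseline and halve the effect, with simulated power of 35% at rho 0.5 and 9% at 0.9. Section E names no contrast, but the first hypothesis is stated against placebo and the design is 2x2, so a between-group reading is the fair one.
- *That a 10% fall is a success rule.* It is an expectation, and glucose is not one of the two powered endpoints.
- *That screening is certainly the OGTT baseline.* The Abstract speaks of a baseline OGTT. The Study Endpoints wording and the schedule favour screening, but the schedule's layout is damaged in the text available.

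**Conclusion.** The point holds as one of efficiency and clear interpretation, not validity. For visceral fat volume, SSPG and the OGTT outcomes, the stated method reduces to a change-score test. Baseline-only adjustment in a 60-subject model lowers variance by about 24%, 13%, 8% and 3% at assumed rho of 0.5, 0.7, 0.8 and 0.9, with little or no gain for 2-hour glucose. These figures assume equal variance at the two times and no dropout.

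The 10% expectation cannot indicate a drug effect while it is worded against baseline. If screening is the baseline, an untreated fall of roughly 2% to 12% is possible for source means of 120-140 mg/dl, SDs of 35-40 and rho of 0.5-0.85, none of which the Protocol gives. Selection explains a fall of 10% or more only at the upper end of that range.

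**What to change.** In section E, replace repeated-measures ANOVA for visceral fat volume, SSPG, 2-hour glucose and glucose AUC with one 2x2 ANCOVA over all 60 subjects. Regress the follow-up value on its own baseline, rhGH, pioglitazone and their interaction. Add only those matching factors that are prespecified and expected to be prognostic. If screening is the OGTT baseline, enter screening 2-hour glucose once, not twice, in the 2-hour glucose model. Keep repeated measures for fasting glucose and HbA1c.

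State that treatment conclusions rest on between-group contrasts. In Study Endpoints, say which OGTT is the baseline and restate the 10% expectation as a difference from placebo.

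The cost is about a paragraph, with no extra data or patient burden. The statistical price is a few degrees of freedom: about 2% in variance for the baseline covariate (factor 1.0185), already counted above. Adding four uninformative factors as well leaves variance about 5% above the change score at rho 0.9.

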**SUPPORTING INFORMATION: Trial Protocol**

# Effects of rhGH and Pioglitazone in Viscerally Obese Adults with IGT

A. **ABSTRACT**

People with impaired glucose tolerance (IGT) who lose visceral fat also tend to lower their risk of developing diabetes. This benefit occurs because visceral fat reduction improves insulin sensitivity and reduces postprandial glucose levels. Thiazolidinediones (TZDs) and growth hormone (rhGH) taken independently foran *extended period of time* can reduce visceral fat and improve endogenous insulin sensitivity. However, in the *short-term* (ie: first 6 weeks of treatment) rhGH may increase insulin resistance. In contrast, a TZD added to rhGH prevents short-term rhGH-induced insulin resistance in experimental animals, suggesting a possible therapeutic benefit with this drug combination in humans. In addition, like rhGH, TZDs mediate some of their insulin sensitizing effects by reducing visceral fat depots. It is therefore possible that the addition of a TZD with standard growth hormone therapy will optimize the short-term and long-term improvements in body composition, insulin sensitivity and glucose metabolism in humans.

The specific aims of this study are as follows: (1) to assess the effects of TZDs with and withoutrhGH on visceral fat content, insulin sensitivity and postprandial glucose levels in viscerally obese subjects with IGT; *and* (2)to compare the effects of TZDs *plus* rhGH with rhGH alone on short-term glucose metabolism. Sixty adult men and women between the ages of 40 and 75 will be recruited to participate and will receive a TZD and rhGH in a double-blind manner. During weeks 0-4, a “run-in” period, subjects will receive a TZD or oral placebo. During weeks 5-40, a TZD or oral placebo will be co-administered with rhGH or a subcutaneous placebo in a 2 X 2 study design. Short-term glucose metabolism will be monitored using fasting glucose levels. Changes in visceral fat content will be quantified using abdominal CT scanning and anthropometric measurements. At baseline and after 9 months of combination drug or placebo treatment, serum postprandial glucose levels will be measured using a standard oral glucose tolerance test, and endogenous insulin sensitivity will be measured using a hyperinsulinemic euglycemic clamp.

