It is expected that the combined use of a TZD and rhGH will be more efficacious in reducing visceral fat quantity and improving insulin sensitivity in viscerally obese adults with IGT compared with the use of either drug alone. The potential long-term benefit of this finding is a reduction in the incidence of type 2 diabetes in populations at high risk of developing diabetes, such as individuals with visceral obesity and IGT.

B. **HYPOTHESES AND SPECIFIC AIMS TO TEST HYPOTHESES**

***Hypothesis #1:*** Subjects who receive rhGH and pioglitazone for 9 months will achieve greater visceral fat reduction, improved insulin sensitivity and lower postprandial glucose levels compared with subjects who receive placebo.

***Specific aim to test hypothesis #1:*** We will assess the effects pioglitazone with and without prolonged rhGH administration on visceral fat change and determine whether change in visceral fat quantity is associated with changes in endogenous insulin sensitivity and postprandial serum glucose levels.

***Hypothesis #2:***Subjects who receive pioglitazone *and* rhGH will demonstrate less transient worsening in glycemic control during the first 6 weeks of treatment compared with subjects who receive rhGH alone.

***Specific aim to test hypothesis #2:***We will compare the effects of a TZD *plus* rhGH with rhGH alone on short-term glucose metabolism. In doing so, we will also determine whether the co-administration of a TZD can effectively counteract the expected transient rise in insulin resistance associated with rhGH and help to maintain better short-term postprandial glucose control compared with rhGH alone.

C. **BACKGROUND**

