TZDs therefore may improve endogenous insulin sensitivity via several mechanisms, including PPAR gamma activation and increased expression of GLUT proteins in adipocytes and perhaps skeletal muscle and other tissues. In addition, a TZD called pioglitazone appears to improve insulin sensitivity by at least one additional very interesting mechanism: shifting or redistributing body fat from visceral fat depots to subcutaneous fat depots. Miyazaki and colleagues noted this finding in a recent study involving the treatment of insulin-resistant type 2 diabetics with pioglitazone (29a). In this study, 16 weeks of treatment with pioglitazone resulted in a reduction in visceral fat area of 9 % at L 4-5 compared to baseline (P <0.05) and a decline in the visceral fat: subcutaneous fat ratio of 25% at L 4-5 compared to baseline (P <0.01) (29a). The shift in fat content from the viscera to the periphery after 16 weeks of pioglitazone treatment was also associated with a statistically significant increase in hepatic insulin sensitivity in the postabsorptive state and higher total body glucose disposal rates as measured by the insulin clamp technique.

In summary, either rhGH or a TZD taken for a prolonged period can reduce visceral fat and improve endogenous insulin sensitivity. However, no human trials to date have prospectively assessed the combined effects of rhGH and a TZD over an extended period on visceral fat change, insulin sensitivity, and glucose homeostasis. It is anticipated that the combination of a TZD and rhGH will have an additive or synergistic effect in improving body composition and glucose homeostasis compared with either drug alone. This in turn would be very efficacious in delaying or preventing type 2 diabetes in viscerally obese adults IGT. It is also anticipated that TZDs will counteract the *transient* insulin antagonizing effects of rhGH and therefore allow this potent drug combination to be used to achieve its long-term benefits.

This protocol would be the first to test the hypothesis that viscerally obese IGT subjects who receive pioglitazone *and* rhGH will demonstrate at least 2 very important benefits: (a) in the short-term, less *transient* worsening in glycemic control compared with subjects who receive rhGH alone; and (b) in the long-term, a greater *reduction* in visceral fat quantity, insulin resistance and postprandial glucose levels compared with placebo or rhGH given alone.

D. **RESEARCH PLANS**

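### Two primary endpoints are each tested at P < 0.05 with no rule on whether one or both must succeed; if either is enough, the chance of a false significant primary result is about 9–10%, not 5%.

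*Protocol*

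**What the plan says.** The sample-size paragraph of the protocol's Experimental Design section states: "we have powered our study based on 2 primary efficacy endpoints as follows". It gives 12 per group for 80% power on visceral fat volume and 15 per group for 80% power on insulin sensitivity, and adopts 15 in each of four groups.

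Hypothesis 1 (section B) is that subjects on rhGH and pioglitazone "will achieve greater visceral fat reduction, improved insulin sensitivity and lower postprandial glucose levels compared with subjects who receive placebo". The Abstract also expects the combination to do better "compared with the use of either drug alone", and the end of the Background section expects a long-term benefit "compared with placebo or rhGH given alone". Hypothesis 2 compares the combination with rhGH alone on short-term glycemic control.

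Section E analyses visceral fat, insulin sensitivity and glucose measures by repeated-measures ANOVA, uses the t test for baseline comparisons, and closes with the only decision rule: "results will be considered significant at *P* < 0.05". The protocol does not rank the two primaries, name a primary contrast among the four groups, say whether one or both endpoints must succeed, or give a testing order or adjustment.

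**The concern.** A flat 0.05 limits the error of each test. It limits the error of the trial's main conclusion only if that conclusion rests on one test, or if every primary must succeed. With two primaries and no success rule, a reader of the results cannot tell which applies. If visceral fat were significant and insulin sensitivity were not, or the reverse, nothing in the protocol would prevent the single positive result from being presented as the trial's success. The stated 5% would then not describe the risk taken. The open choice also affects power: if both endpoints are required, powering each one separately at 80% does not give 80% for the pair.

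**Working it through.** **The protocol's own figures.** It states no overall error rate, only 12 and 15 per group for 80% power. These sample sizes cannot be reproduced from the quoted effects (17.9 ± 3.5 percent; 1.2 ± 0.6, given as ± 0.7 in the Background), because the spread is not identified as SD or SE.
- Read as SD, the two-sample and paired formulas give 1 per group for visceral fat and 2 to 6 for insulin sensitivity.
- Read as SE, visceral fat gives 12 only if the source study had about 19 subjects (an assumption). Insulin sensitivity gives 32 or more for source sizes of 8 to 30.

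This does not touch the error-rate calculation. For power I therefore use the standardized effects that the stated sample sizes imply (two-sample t test, two-sided 0.05, 80%): 1.197 for visceral fat at n = 12 and 1.060 for insulin sensitivity at n = 15.

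**Inputs for the error rate.** Two primaries, four groups of 15 and P < 0.05 per result are from the protocol. Two-sided testing and an endpoint correlation of 0 to 0.5 are assumptions.

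**Either endpoint is enough, one test each.**
- Independent endpoints: 1 − (1 − 0.05)² = 9.75%.
- Simulated under no effect, combination versus placebo, correlation 0 to 0.5: 9.1–10.0% in one run; 9.8% falling to 8.9% in another with pooled variance.
- Overall F test across the four groups, one per endpoint: 9.2–9.9%. This is the closest match to section E. Each primary is measured only at baseline and at the end (CT at week 40, insulin sensitivity test at week 43), so the group-by-time test amounts to one comparison of changes across groups.
- Counting only results that favour the combination: 1 − (1 − 0.025)² = 4.9%, or 4.6% at correlation 0.5, against 2.5% for one test.

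**Both endpoints required on one contrast.** If both nulls are true, the rate is 0.05² = 0.25% with independent endpoints and rises to 5% with perfectly correlated ones. If only one null is true, it is still at most 5%.

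**Combination against each of the other three groups, unprotected, on both endpoints.**
- One endpoint: 12.3%.
- Two independent endpoints: 1 − (1 − 0.123)² ≈ 23%. Over correlation 0 to 0.5, simulations give about 22–24%.
- Favourable results only: about 11–12%.

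**Power at 15 per group, implied effects.**
- Each endpoint alone at 0.05: visceral fat about 88.6%, insulin sensitivity 80%.
- Both required, independent: 0.886 × 0.80 ≈ 71%.

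| Rule over the two primaries | Visceral fat | Insulin sensitivity |
|---|---|---|
| Each at 0.05 (as written) | 88–89% | 80% |
| Fixed order, visceral fat first | 88–89% | 71–74% |
| Holm | 85–86% | 77–78% |

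The ranges in the last two rows cover correlation 0 to 0.5. Bonferroni at 0.025 each would leave insulin sensitivity at about 70%.

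**The case against.** **Joint success.** Hypothesis 1 joins its outcomes with the word and, and the design takes the larger of the two sample sizes. That could mean that both endpoints must succeed, in which case the error rate is at most 5%. The reading is fair and the text does not exclude it. But the protocol never states it as the success rule, and the sample size was not set for it: power for both is about 71% if the endpoints are independent. Either reading leaves something to settle.

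**The SAP.** Contrasts and adjustments are often left to an SAP, which may exist here. So the absence of detail is not the complaint. The complaint is the rule that section E does state, 0.05 for all results, set beside two named primaries. An SAP that repaired this would still have to be squared with the protocol.

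**Stronger readings that the protocol does not support.**
- A reader might infer an overall error of 22–24%. That needs three unprotected pairwise comparisons per endpoint. Section E names ANOVA for the outcomes and the t test only for baseline values. Superiority over pioglitazone alone appears as an expectation or possibility, not in either formal hypothesis.
- A reader might call 9–10% the chance of a false efficacy claim. It counts errors in both directions; for results that favour the combination the figure is about 5%.
- A reader might infer that any significant comparison counts as success. Section E defines when a result is significant, not when the trial succeeds.

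**Conclusion.** The point holds in a limited, conditional form. The protocol applies P < 0.05 to every result while naming two primary endpoints and no success rule. If either endpoint is enough, the chance of a false significant primary result is about twice the nominal level: 9–10% against 5% in both directions, or about 5% against 2.5% in favour of the combination. This assumes two-sided tests, one test per endpoint, and endpoint correlation of 0 to 0.5. It holds for the overall F test as well as for a single pairwise contrast. If both endpoints are required, the 5% level holds but joint power is not assured at 80%. The protocol should say which rule applies.

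**What to change.** In section E of the protocol:

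1. Name combination versus placebo, the Hypothesis 1 comparison, as the primary contrast for both primary endpoints.
2. Control the two-sided 5% level over visceral fat and insulin sensitivity, either by Holm (the smaller P against 0.025, then the other against 0.05) or by a fixed order (visceral fat at 0.05, then insulin sensitivity at 0.05 only if visceral fat is significant).
3. Treat the other group comparisons and postprandial glucose as secondary.
4. Keep Hypothesis 2, combination versus rhGH alone on short-term fasting glucose, as a separate, pre-named test at 0.05. Labelling fasting glucose secondary with no claim of significance would remove one of the protocol's two formal hypotheses.

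**Cost.** A few sentences and no extra subjects. Insulin-sensitivity power falls from 80% to about 77–78% with Holm or 71–74% with the fixed order. Visceral-fat power stays at 88–89% with the fixed order or falls to 85–86% with Holm. The fixed order is therefore cheaper for visceral fat and Holm for insulin sensitivity; under the fixed order, insulin sensitivity cannot be claimed if visceral fat fails. Postprandial glucose, part of Hypothesis 1, loses confirmatory standing. The 5% then covers the two primaries, not the primaries and Hypothesis 2 together: if those two were independent, the joint figure would be at most 1 − 0.95² = 9.75%, and the protocol should say that this is intended.
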